## Abstract

**Background:**

Although of high individual and socioeconomic relevance, a reliable prediction model for the prognosis of juvenile stroke (18–55 years) is missing. Therefore, the study presented in this protocol aims to prospectively validate the discriminatory power of a prediction score for the 3 months functional outcome after juvenile stroke or transient ischemic attack (TIA) that has been derived from an independent retrospective study using standard clinical workup data.

**Methods:**

PREDICT-Juvenile-Stroke is a multi-centre (*n* = 4) prospective observational cohort study collecting standard clinical workup data and data on treatment success at 3 months after acute ischemic stroke or TIA that aims to validate a new prediction score for juvenile stroke. The prediction score has been developed upon single center retrospective analysis of 340 juvenile stroke patients. The score determines the patient’s individual probability for treatment success defined by a modified Rankin Scale (mRS) 0–2 or return to pre-stroke baseline mRS 3 months after stroke or TIA. This probability will be compared to the observed clinical outcome at 3 months using the area under the receiver operating characteristic curve. The primary endpoint is to validate the clinical potential of the new prediction score for a favourable outcome 3 months after juvenile stroke or TIA. Secondary outcomes are to determine to what extent predictive factors in juvenile stroke or TIA patients differ from those in older patients and to determine the predictive accuracy of the juvenile stroke prediction score on other clinical and paraclinical endpoints. A minimum of 430 juvenile patients (< 55 years) with acute ischemic stroke or TIA, and the same number of older patients will be enrolled for the prospective validation study.

**Discussion:**

The juvenile stroke prediction score has the potential to enable personalisation of counselling, provision of appropriate information regarding the prognosis and identification of patients who benefit from specific treatments.

**Trial registration:**

The study has been registered at https://drks.de on March 31, 2022 (DRKS00024407).

## Background

With an annual mortality rate of about 6.55 million and the loss of 143 million disability-adjusted life-years, stroke is ranked the second leading cause of death worldwide and is one of the most frequent causes of disability in adults [1]. While the incidence of stroke increases with age, about 15% of strokes occur in persons younger than 55 years [2], i.e. juvenile stroke, and of particular note is that the incidence of juvenile stroke increased up to 40% over the last decades [3]. Underlying aetiologies of stroke differ between younger and older patients and in juvenile stroke rare and cryptogenic causes are frequent with a range of 50% [4]. Due to the young age and longer life expectancy in juvenile stroke, the prognosis and therefore counselling differs from that in older patients. The long-term medical, psychosocial and socioeconomic consequences are particularly severe in this young age group [5]. Therefore, the identification of risk factors and the development and validation of a reliable prediction score for the outcome after juvenile stroke or transient ischemic attack (TIA) are urgently needed. To date there is no study that prospectively validates a model that predicts functional outcome after juvenile stroke. The PREDICT-Juvenile-Stroke study (https://drks.de; DRKS00024407) presented in this protocol aims to fill this gap by prospectively validating a juvenile stroke prediction score for the 3 months functional outcome that has been derived from an independent retrospective cohort study, using a combined set of clinical and paraclinical data.

## Methods/design

### Design

The PREDICT-Juvenile-Stroke study presented in this protocol is a multi-centre, prospective observational cohort study on juvenile stroke or TIA. Patients are enrolled at the participating study sites at the university hospitals of the Ludwig-Maximilians University Munich, the Technical University Munich, the Eberhard Karls University Tübingen and the Ulm University Medical Center in Germany. The study records clinical routine data of newly diagnosed ischemic stroke or TIA patients according to current diagnostic criteria [6, 7] and involves phenotypic characterization over 3months including brain imaging as well as prospective biosample collection (Fig. 1). During the in-hospital stay routinely collected data including demographic data, clinical parameters as well as paraclinical data from examinations necessary within the framework of clinical workup (e.g., CT, MRI, doppler/duplex sonography, transthoracic echocardiography, veinpuncture, lumbar puncture) are recorded. Standardized clinical follow-up is assessed 3 months after stroke either as a routinely arranged outpatient visit or by a structured telephone interview. In each of the centres, the study uses a specific uniform IT-infrastructure (already established within the DIFUTURE consortium [8], supported by the BMBF grants 01ZZ1804A, 01ZZ1804B, 01ZZ1804C, 01ZZ1804D and 01ZZ1804I) in which clinical process data are transformed into structured data usable in clinical research. The recruitment phase lasts 3 years (Table 1). The derived data will be used to validate a juvenile stroke prediction score, which has been developed based on monocentric retrospective data of 340 juvenile stroke and TIA patients who were hospitalized at the stroke unit of Ludwig-Maximilians University Munich between Jan 01, 2011, and Mar 31, 2020. The score is based on predictor variables that are divided into 4 categories: preadmission factors; clinical, imaging and laboratory findings at admission; results of diagnostic investigations during the in-hospital stay and treatment given at admission or discharge; and is of high predictive value (area under the curve (AUC) 96.4%). As the binary parameter “ischemic stroke vs. TIA” did not improve outcome prediction, both stroke as well as TIA patients are enrolled in the presented study. Furthermore, prospective data will be used to determine to what extent variables included in the score differ from predictive factors in older stroke or TIA patients and determine the additive value of the new juvenile stroke prediction score compared to established age-independent prediction models. Another aim of the PREDICT-Juvenile-Stroke study is the assessment and prediction of quality of life in patients with juvenile stroke and older stroke patients. To characterize disease effect on quality of life, patient-reported outcome measures are assessed during the in-hospital stay and at the 3 months follow-up. These data will give new insights of modern therapies in stroke with respect to their long-term impact on quality of life.

**Fig. 1 Fig1:**
[figure not shown]
Graphical study design

**Table 1 Tab1:** Timeframe of the study

Study Phase	Tasks	2023				2024				2025				2026			
		quarter (proposed trial duration)															
		Q1	Q2	Q3	Q4	Q1	Q2	Q3	Q4	Q1	Q2	Q3	Q4	Q1	Q2	Q3	Q4
Execution	Screening and inclusion period																
	3 months follow-up																
	possible extended Follow-Up																
Analysis	Final data analysis																
	preparataion of manuscript																

### Patient population – inclusion and exclusion criteria

On admission to the hospital, patients with acute ischemic stroke or TIA are screened for participation in the study.

### Inclusion criteria

Juvenile stroke patients aged 18–55 years and older stroke patients > 55 years, both patients with first-ever strokes as well as with recurrent events can be enrolledWritten informed consent by the patient or their legal representatives obtained at the latest prior to the 3 months follow-up

### Exclusion criteria

The patient is directly involved in the conduct of the protocolRefusal of consent

Written informed consent can be obtained latest prior to the 3 months follow-up. As all information are collected as part of clinical routine, patients can be enrolled, and information be recorded even if patients are incapable of providing consent and no legal representative is available. If patients are lost to follow-up or die before informed consent can be obtained, the recorded data are kept within the study database in a de-identified manner.

### Treatment or intervention

Treatment decisions are entirely the responsibility of the treating physician and must follow state of the art best-practice rules.

### Primary outcomes

The primary objective is to prospectively validate the clinical potential of a juvenile stroke prediction score. Treatment success at 3 months is defined as mRS (modified Rankin Scale) [9] 0–2 or return to baseline pre-stroke mRS.

### Secondary outcomes

Secondary outcomes are to determine to what extent predictive factors in juvenile stroke or TIA patients differ from those in older patients, to correlate the juvenile stroke prediction score with secondary clinical and para-clinical endpoints (e.g. recurrent ischemic stroke or TIA or haemorrhagic stroke) and to determine its predictive accuracy with respect to these secondary endpoints.

A non-clinical objective is also to assess the properties and functionality of data flows implemented with the IT-infrastructure.

Demographic and clinical data to be collected (Fig. 1):

The following parameters are included in the juvenile stroke prediction model and are therefore collected to validate the model:Preadmission factors (age, CHA_2_DS_2_-VASc-Score)Clinical, imaging and laboratory findings at admission (National Institutes of Health Stroke Scale (NIHSS), Alberta stroke programme early CT score (ASPECTS), glucose level))Results of diagnostic investigations during the in-hospital stay (mean intima-media thickness on ultrasonography, underlying aetiology)treatment given at admission or discharge (intravenous thrombolysis, reperfusion success measured by the modified Thrombolysis in Cerebral Infarction (mTICI) score, antithrombotic therapy given at discharge)

Additionally, the following data are collected for further research during the in-hospital stay:Demographic data (gender, ethnicity)Medical/surgical history (pre-existing illnesses/previous operations, cardiovascular risk factors, signs and symptoms, onset of symptoms, premorbid mRS)Relevant concomitant treatment (type of therapy, name of medication, daily dosage and duration for such use)family history (positive family history defined as cardiovacular event in a first-degree relative < 65 years)Neurological examination (NIHSS after 24 hours as well as at discharge)Vital signs (blood pressure, heart rate, oxygen saturation, blood glucose)Patient-reported outcome measures (clinical global impression)

The following parameters are collected 3 months after index stroke:Medical/surgical history (new illnesses, operations that have taken place during the interval, cardiovascular risk factors, current signs and symptoms, mRS)Relevant medication (type of therapy, name of medication, daily dosage and duration for such use)Patient-reported outcome measures (clinical global impression, EuroQol – Visual analogue scale)Questionnaires on quality of life and depression (Beck-Depression-Inventory, EuroQol 5 dimensions with 5 response levels)Cognitive assessment (Montreal Cognitive Assessment (MoCA))Neurological examination (NIHSS)Vital signs

Paraclinical parameters to be documented:ElectrocardiogramLaboratory analysesNeuroimaging (cerebral CT/CT angiography, CT perfusion, MRI, MR angiography)Digital subtraction angiography (DSA)Additional imaging modalities (e.g., X-ray, positron emission tomography)Doppler/duplex sonographyElectroencephalographyTransthoracic echocardiography/ transoesophageal echocardiographyLong-term electrocardiogramCancer screening (e.g. X-ray, CT-thorax/abdomen, gynecologic/dermatologic examination)Loop-recorder implantationQuestionnairesCSF analysisAdditional laboratory analyses

There is a variety of types of data and parameters which are documented if the respective examinations are necessary within the framework of clinical workup. For all procedures we assess if it is performed and if so, document the results.

### Biosamples

Patients can optionally agree to an additional collection of biomaterial (blood/CSF) at baseline as well as, if possible, at the 3 months follow-up visit as part of the routine diagnostic procedure (e.g. veinpuncture, lumbar puncture). One part of biosamples obtained from the patients is used for routine analysis. Here, clinical-chemical parameters, hematological examinations, functional characteristics and coagulation tests are performed. The other part is biobanked for biomarker studies, primary cells are isolated and cryopreserved. As a secondary objective we will analyse the predictive relevance of established biomarkers in the field like copeptin, serum neurofilament light chain, growth differentiation factor 15, S100, N-terminal pro-B-type natriuretic peptide, atrial natriuretic peptide and fatty acid-binding protein on treatment success and the 3 months functional outcome.

Further possible biomarkers are genome, epigenome, metabolome, proteome and transcriptome markers as well as parameters of morphological analytics and in vitro studies on isolated cells. Methods for analyzing proteins are among others ELISA, mass spectrometry and 2-dimensional gel electrophoresis. Methods for the analysis of RNA and DNA are for example polymerase chain reaction, microarray and sequencing. The metabolome and lipidome can be assessed with mass spectrometry.

### Data monitoring body

As all information are collected within the framework of clinical routine, no central data monitoring body is installed. Staff in the respective Neurology Departments is regularly trained and certified in the use of standardized scales and scores (e.g. National Institutes of Health Stroke Scale i.e. NIHSS and modified Rankin Scale, i.e. mRS). Data sets will automatedly be checked for plausibility before the final analysis. Federated privacy-preserving record-linkage is used to control for duplicates in the differing databases.

### Sample size estimates

The primary endpoint will be analysed by determining the receiver operating characteristic curve (ROC) and its AUC. We want to reject the null hypothesis: AUC ≤ 0.7. Assuming a true AUC of 0.8 and a treatment success rate of 0.7 a total of 344 patients is needed (power 90%, level of significance 5%). To compensate for possible missing data a minimum of 430 juvenile stroke/TIA patients aged 18 to 55 years will be included in the study (estimated 25% missing rate). To assess differences in predictive factors between juvenile and older stroke/TIA patients, the same number of older patients above 55 years will be included. However, the calculated number only provides the minimum number of patients for validation of the prediction score. We will include all eligible patients to increase power and facilitate further research. As about 100 juvenile acute stroke/TIA patients are treated annually in each of the participating stroke units, we expect to screen about 1200 juvenile stroke/TIA patients for inclusion in the study during the recruitment phase of 3 years.

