### Statistical analyses

In order to test the null hypothesis, we use the 95% confidence interval of the AUC. The null hypothesis will be rejected if the value of 0.7 is not contained in the corresponding 95% confidence interval.

Additionally, the calibration curve and the Brier score will be calculated to assess calibration. We will also analyse the predictive value of the score with respect to alternative clinical and paraclinical outcome variables using the AUC of the ROC, calibration curves and the Brier score. According to data type, distributions and proportions will be compared and regression models will be fitted to identify age-related differences.

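### The 25% missing-data allowance was applied as 344 × 1.25; the resulting juvenile minimum of 430 covers only 20% missing data (minor arithmetic correction)

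*Protocol article*

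**What the plan says.** All the figures are in the protocol article under Sample size estimates. The hypothesis is "We want to reject the null hypothesis: AUC ≤ 0.7". The base size follows: "Assuming a true AUC of 0.8 and a treatment success rate of 0.7 a total of 344 patients is needed", at 90% power and a 5% significance level. The allowance comes next: "To compensate for possible missing data a minimum of 430 juvenile stroke/TIA patients aged 18 to 55 years will be included in the study", with the reason in brackets, "estimated 25% missing rate".

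The Methods part of the abstract repeats the figure ("A minimum of 430 juvenile patients") and, like the sample size section, sets the older cohort at the same number.

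The sample size section also describes 430 as a minimum only. It says that every eligible patient will be included, and it expects about 1200 juvenile patients to be screened over three years. The decision rule is under Statistical analyses: "The null hypothesis will be rejected if the value of 0.7 is not contained in the corresponding 95% confidence interval".

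**The concern.** Three printed figures do not agree: 344 needed, 25% missing, 430 enrolled. A missing rate is ordinarily a share of the patients enrolled. To end with 344 analysable patients, the enrolment must then be 344 divided by the share that remains, not 344 increased by a quarter.

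The figure 430 is the only enrolment number to which the study commits. If recruitment ended there and the plan's own missing rate came true, the primary analysis would have fewer patients than the plan says it needs.

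The allowance is likely to be used. The score needs items from routine workup, such as mean intima-media thickness and reperfusion grade. The article says that examinations are documented where the clinical workup requires them, and it foresees patients who are lost to follow-up or die before consent can be obtained.

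**Working it through.** **Inputs** (Sample size estimates, unless noted): null AUC 0.7; assumed AUC 0.8; success rate 0.7, so 30% unfavourable; power 90%; significance level 5%; required N 344; missing rate 25%; minimum enrolment 430. The decision rule is a 95% confidence interval (Statistical analyses), so two-sided 5% is used below.

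**1. Where 430 comes from**
- 344 × (1 + 0.25) = 430 exactly.
- 344 / 430 = 0.80, so 430 is the right enrolment for 20% missing.

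**2. What 25% missing requires**
- 344 / (1 − 0.25) = 458.7, rounded up to 459.
- Check: 459 × 0.75 = 344.25, which is enough; 458 × 0.75 = 343.5, which is not.
- Difference from the stated minimum: 459 − 430 = 29.

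**3. What 430 delivers at 25% missing**
- 430 × 0.75 = 322.5, so 322 to 323 analysable patients.
- Shortfall: 344 − 322.5 = 21.5, about 6% of 344.

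**4. Reproducing the base size of 344**

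The article does not name its method. Take the Hanley-McNeil variance with n₁ patients in the positive class and n₀ in the other:

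Var(A) = [A(1−A) + (n₁−1)(Q₁−A²) + (n₀−1)(Q₂−A²)] / (n₁n₀), with Q₁ = A/(2−A) and Q₂ = 2A²/(1+A).

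Power = Φ[(0.8 − 0.7 − 1.960 × SE₀) / SE₁], with SE₀ at AUC 0.7 and SE₁ at AUC 0.8.

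With the 30% unfavourable outcome as the positive class, the smallest N with 90% power is 342, within 1% of 344. At N = 344, SE₀ = 0.03228 and SE₁ = 0.02833, so (0.1 − 0.06327) / 0.02833 = 1.297 and power is 90.3%. An Obuchowski variance taken at the null, with a 70% positive class and two-sided 5%, gives N = 347. The Hanley-McNeil and Obuchowski variants at one-sided 5% and 90% power gave 310 at most and do not reproduce 344.

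**5. Power at the floor**

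| Assumption | Power at 322 to 323 |
|---|---|
| Hanley-McNeil, unfavourable outcome as positive class (N = 342) | 88.1 to 88.2% |
| Obuchowski, null variance, 70% positive class (N = 347) | 87.8 to 87.9% |
| 344 taken to give exactly 90%, two-sided 5%, SE ∝ 1/√N | 88.0 to 88.1% |
| Hanley-McNeil, success as positive class (N = 260; does not reproduce 344) | 95.6 to 95.7% |
| Binormal simulation with DeLong 95% intervals (an added assumption) | about 93 to 95% |

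The first row at N = 322: SE₀ = 0.03337 and SE₁ = 0.02928, so (0.1 − 0.06541) / 0.02928 = 1.181 and power is 88.1%. The third row at 322.5: (1.960 + 1.282) × √(322.5/344) − 1.960 = 1.179, power 88.1%.

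The last two rows do not contradict the others. Under those assumptions fewer patients are needed for 90% power, so a loss of 22 still leaves power above target.

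**The case against.** **The figure is only a floor.** The plan says so, includes all eligible patients, and expects to screen about 1200. Reaching 430 takes 35.8% of 1200 (430/1200), and 459 takes 38.3% (459/1200). Nothing in the article stops recruitment at 430. This stands, and it is the main reason to grade the point as minor. It does not make the figure right: 1200 is a number screened, not enrolled or analysable, and 430 is what the plan guarantees.

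**The power loss depends on the formula.** A reader might infer that 430 leaves the trial underpowered. The article does not support that as an unconditional statement. It names no variance method, and two of the assumptions above keep power at 322 well above 90%. The shortfall against 344 patients is plain arithmetic; the shortfall against 90% power holds only relative to a planning model that yields about 344.

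**The rate may have been meant as a surcharge.** If 25% means missing patients relative to complete ones, 86/344 = 25% and 430 is consistent. This is the less usual meaning of a missing rate, and the article gives no such definition. On that reading the defect is one of labelling, and the wording still needs correcting, because most readers will compute 322.

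**The older cohort.** A reader might also infer that each cohort is 29 patients short. The article gives the older cohort no hypothesis test, power target or required analysable number of its own; it only ties that cohort to the juvenile figure. The 29 applies to the juvenile cohort alone.

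**Conclusion.** The inflation step is wrong as written. With a 25% missing rate taken as a share of enrolled juvenile patients, 344 analysable patients require 459 enrolled. The stated 430 covers 20% missing and, at 25%, leaves about 322, which is 21 to 22 too few.

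The consequence is small. Under planning models that come close to 344, the loss is about 2 percentage points of power (90% to about 88%), and it arises only if enrolment ends near the minimum. The error does not bias the AUC estimate or change the error rate or the endpoint. This is a minor correction of a stated figure, and not evidence that the primary analysis will be underpowered.

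**What to change.** Make the figures agree in the sample size section and in the Methods part of the abstract, in one of three ways:

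- State the juvenile minimum as 459 (344 / 0.75) and keep the 25% missing rate.
- Keep 430 and state that it allows for 20% missing data, if that rate can be justified.
- Keep both 430 and 25%, and state that about 322 patients are then expected to be analysable, with the power at that number under a named variance method.

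Whichever is chosen, say that the rate is a share of enrolled patients. If the juvenile minimum changes, state whether the older cohort follows it; it would do so only because the plan links the two numbers.

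The cost is a change of wording. Even the first option should add little or no recruitment effort, because all eligible patients are to be included and about 1200 are expected to be screened.

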### Statistical analyses

In order to test the null hypothesis, we use the 95% confidence interval of the AUC. The null hypothesis will be rejected if the value of 0.7 is not contained in the corresponding 95% confidence interval.

Additionally, the calibration curve and the Brier score will be calculated to assess calibration. We will also analyse the predictive value of the score with respect to alternative clinical and paraclinical outcome variables using the AUC of the ROC, calibration curves and the Brier score. According to data type, distributions and proportions will be compared and regression models will be fitted to identify age-related differences.

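### Calibration curves and Brier scores are planned for outcomes other than the one whose probability the score predicts, with no stated recalibration

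*Protocol article*

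**What the plan says.** The abstract of the protocol article (Methods) defines what the score delivers: the patient's "individual probability for treatment success defined by a modified Rankin Scale (mRS) 0–2 or return to pre-stroke baseline mRS", at 3 months. The Primary outcomes section defines treatment success in the same way.

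The Secondary outcomes section adds further clinical and paraclinical endpoints, with "recurrent ischemic stroke or TIA or haemorrhagic stroke" as examples. It aims to correlate the score with them and "to determine its predictive accuracy with respect to these secondary endpoints".

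The Statistical analyses section names the measures. For the primary endpoint, beside the AUC, "the calibration curve and the Brier score will be calculated to assess calibration". The predictive value of the same score is then to be examined for "alternative clinical and paraclinical outcome variables using the AUC of the ROC, calibration curves and the Brier score". Neither section mentions refitting or recalibrating the score for another outcome, and no event rates are given for the secondary endpoints.

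**The concern.** A calibration curve asks whether, among patients given probability p of an event, a fraction p have that event. The Brier score is the mean squared distance between a predicted probability and the 0/1 outcome it predicts. Both need a prediction of the event being scored. The AUC does not, because it uses only the ordering of patients.

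The plan applies all three measures to events for which the score gives no probability. Read as written, the curve and the Brier score for recurrent stroke would compare the chance of a good functional outcome (or its complement) with the frequency of recurrence. The result would mainly reflect how far the two base rates lie apart and would say little about the score. Predictive accuracy for these endpoints is a declared secondary objective, so a sound score could be reported as badly calibrated for reasons unrelated to its merit.

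There is also a labelling matter. The Brier score responds to discrimination and outcome prevalence as well as to calibration, so describing it as a calibration measure is imprecise even for the primary endpoint.

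**Working it through.** **The plan's own figure.** The point disputes no number. For completeness, the stated 344 patients (AUC 0.8 against 0.7, success rate 0.7, power 90%, 5% level) reproduce closely. The Hanley-McNeil variance, two-sided, with the 30% without success as the positive class, gives 342, and power at 344 is 90.3%.

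**Inputs.** From Sample size estimates: success rate 0.7 and AUC 0.8. Assumed, because the documents are silent: secondary event rates r of 3% to 20%, and the link between the event and the score.

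**Step 1: a score with no fault.** A binormal score with AUC 0.8 and success rate 0.7, perfectly calibrated for success, was simulated (400,000 patients). Its Brier score for success is 0.1583, against 0.7 × 0.3 = 0.21 for a constant prediction. For a calibrated score, Brier = π(1−π) − Var(P), so Var(P) = 0.21 − 0.1583 = 0.0517.

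**Step 2: the same score against another event.** Take the reading more favourable to the plan, in which 1−P serves as the predicted risk of an adverse event. Its mean is 1 − 0.70 = 0.30. If the event is unrelated to the score,

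Brier = r(1−r) + (0.30 − r)² + Var(P).

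At r = 0.05: 0.0475 + 0.25² + 0.0517 = 0.0475 + 0.0625 + 0.0517 = 0.162.

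If the event is related to the score (simulated with its log-odds falling by 0.5 per unit of the score's log-odds of success), the Brier score at r = 0.05 is 0.147.

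| Assumed event rate | Mean of 1−P | Brier of 1−P, unrelated event | Brier of 1−P, related event | Constant prediction r(1−r) | Recalibrated, related event |
|---|---|---|---|---|---|
| 3% | 0.30 | 0.154 | 0.144 | 0.0291 | 0.0289 |
| 5% | 0.30 | 0.162 | 0.147 | 0.0475 | 0.0466 |
| 10% | 0.30 | 0.182 | 0.154 | 0.0900 | 0.0863 |
| 20% | 0.30 | 0.222 | 0.174 | 0.160 | 0.149 |

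The third column is the formula above with r replaced; the related-event columns are simulated. In every row the unchanged score does worse than a constant, although it is faultless for its own outcome. Once the prediction is mapped to the new event, its Brier score falls just below the constant's.

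**Step 3: the Brier score as a calibration measure.** With perfect calibration throughout and 70% success, the simulated Brier score is 0.205, 0.188, 0.158, 0.113 and 0.066 at AUC 0.6, 0.7, 0.8, 0.9 and 0.964. It changes about threefold while calibration stays perfect, so it is an overall accuracy measure with a calibration component.

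**The case against.** The best defence is that the article never says the raw success probability will be used unchanged. The secondary aim speaks of correlating the score with other endpoints. An analyst could regress each endpoint on the score and then report calibration and Brier score of the fitted risk. That fits the text, and an analysis plan not shown may say so. This stands as far as it goes, and it is why the point is conditional. It does not remove the point: the article states which measures go with which endpoints, two of the three need a mapping, and none is mentioned.

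Three stronger readings are tempting, and the documents do not support them.

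- *All secondary accuracy results are uninterpretable.* They are not. The AUC is planned in the same sentence and remains valid for any binary endpoint.
- *Every alternative endpoint must show gross miscalibration.* The endpoints are given only as examples, and the gap depends on the event rate and on the link to the score. For a related event at 20%, it is 0.174 against 0.160, which is modest.
- *An overconfident score could be passed as calibrated on the primary endpoint.* A reader might infer this from the Brier label together with the development AUC of 96.4% in 340 patients at one centre. But a calibration curve is planned beside the Brier score and would show overconfidence. In a simulated score with AUC 0.803 and the spread of its log-odds doubled, the lowest decile has mean prediction 0.03 against 0.23 observed. Only the label is at fault there.

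**Conclusion.** The point holds in conditional form. Unless the score is recalibrated for each endpoint, the planned calibration curves and Brier scores for alternative outcomes compare a predicted probability with a different event. At an assumed 5% event rate, a score perfectly calibrated for success would show a mean predicted risk of 0.30 and a Brier score of about 0.15 (related event) to 0.16 (unrelated event), against 0.0475 for a constant prediction. These sizes rest on the plan's own AUC of 0.8 and success rate of 0.7, on assumed event rates and on an assumed link to the score. The direction of the mismatch is the same at every rate tried, and its size shrinks as the event rate approaches 0.30.

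The consequence is confined to two measures within a secondary objective. The AUC for binary endpoints, the primary hypothesis test and the sample size are unaffected. For the primary endpoint, what remains is a minor imprecision in calling the Brier score a calibration measure.

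**What to change.** For alternative binary endpoints, choose one of the following and state it in the Statistical analyses section:

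1. Report the AUC only, with its confidence interval; or
2. For each endpoint, first refit the intercept and slope of the score's linear predictor by logistic regression, then report the calibration curve and Brier score of the recalibrated prediction, labelled as recalibrated, with r(1−r) as the reference value for the Brier score.

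The second option has a small drawback. Intercept and slope are estimated in the same data in which calibration is then judged, so the result is not an external validation and should not be described as one. Recalibration that keeps the ranking leaves the AUC unchanged, so nothing is lost there.

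For the primary endpoint, describe the Brier score as overall accuracy and judge calibration from the curve already planned, preferably with calibration-in-the-large and calibration slope and their 95% confidence intervals.

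The cost is a few sentences and a few lines of code. No new data, no extra patients and no change to the primary analysis are needed.
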